**Script for telephone screening is attached as Appendix B.**

**Informed consent form for patients and controls is included in IRB application.**

1. **Study Procedures**

We plan to enroll 35 participants. The study components will consist of an initial phone screen with the participant to verify provisional inclusion criteria. For applicants meeting provisional inclusion criteria, a screening visit will be scheduled for Informed Consent, explanation of study procedures, screening with study instruments and interviews, and an opportunity for a practice session in the mock MRI scanner. For applicants meeting inclusion criteria following screening, a study visit will be scheduled, preferably within 2 weeks of the screening day.

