**Table 1. Visit Schedule**

| **Procedure***** | **Visit 1**  **(day 1)** | **Visit 2**  **(day 2-8)** | **Visit 3**  **(days 5-14)** | **Visit 4-12**  **(days 2-10)** |
| --- | --- | --- | --- | --- |
| Consent | X |  |  |  |
| Surveys/questionnaires***** | X | X | X | X |
| Fitness test* | X | X | X |  |
| EKG | X |  |  |  |
| Vital Signs | X |  |  |  |
| Exercise**,*** |  | X | X | X |
| fMRI**** | X | X | X |  |
| Urine Tests | X | X | X | X |
| Buccal cells or Saliva (DNA) | X |  |  |  |
| Breath test | X | X | X |  |

*VO2max – assessment of physical fitness. This test will be done during Visit #1, #2, or #3.

** exercise in randomized order. The participant will be asked to run or jog on a treadmill at a speed approximately 20-50% lower than your fast running speed and/or walk at a comfortable speed during Visit #4 – Visit #12.

*** - Participant may be asked to come to one, two, three, four, five, or six visits.

**** - functional magnetic resonance imaging (test to picture parts of brain). This will be done twice, either during Visit #1 and Visit #3 or during Visit # 2 and Visit #3.

*****On the days a subject is not scheduled for a visit, we may ask questions from the Marijuana Craving Questionnaire, Caffeine and Nicotine Use questionnaire, and Drug use (question Page 13 Question 1: Marijuana (as a dried plant) over the phone. The subject will get copies of these questionnaires so they will know questions we may ask them.

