**General statistical methods**

Percent BOLD signal change in the targeted ROIs, as well as demographic characteristics of the experimental and control group will be summarized using descriptive statistics. Given proposed group sizes of 10 participants (with no missing data), we expect to use parametric statistical analysis procedures. However, samples of this size are highly sensitive to outlier values, thus visualization and statistical investigations of parametric assumptions will be conducted. Because relative (greater or lesser) differences in activation rather than absolute values of those differences are of primary interest in this research, if distributions do not meet parametric assumptions, depending on the nature of the violations methods based on ranks will be used or outliers will be dealt with on a case-by-case basis.

Assuming multivariate normality and homogeneity assumptions are met, multivariate profile analysis (Tabachnick & Fidell, 2000) will be used to investigate differential patterns of ROI activation (profiles) between the two primary study groups of cannabis users and non-user controls (Primary Specific Aim 1). A statistically significant interaction effect of study group and ROI (e.g., insula, inferior frontal cortex, ventrolateral prefrontal cortex, parahippocampal gyrus, bilateral fusiform gyrus) will indicate statistically significant differences in activation (% BOLD signal change) profiles. Given a statistically significant interaction effect from an overall profile analysis, post-hoc tests controlling the experiment-wise Type I error rate will be used to determine precisely which component members of the profile (i.e., areas of activation or ROIs) are contributing to the overall profile difference, as well as the magnitude and direction of the specific component difference. These effect sizes will be used for statistical powering estimates in the planning of subsequent RO1 research.

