Graphical and descriptive statistical techniques will be used to explore patterns of changes in activation within subjects to cannabis cues after the two exercise conditions (Primary Specific Aim 2). Tests of the changes in activation within key ROIs will be conducted using general linear modeling (GLM) methods that incorporate Generalized Estimation Equations (GEE) for parameter estimation of correlated data. The combination of GLM and GEE provides the most flexibility for modeling data of uncertain distribution, as well as for incorporating the mixed effects of between (cannabis vs. control) and within (prior exercise state). Again, effect sizes generated from these analyses will be used for statistical powering of planned subsequent RO1 research.

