**Power Estimates**

Because this is a pilot study to demonstrate feasibility, we estimate 10 subjects per group as reasonable sample size as this group size is commonly well in fMRI pilot studies. A key outcome of this study will be the calculation of effect sizes that will inform the powering of subsequent, larger studies. Commercially available statistical software packages (NCSS and PASS, number Cruncher Statistical Systems, Kaysville, Utah; SPSS, Chicago, IL; Stata, College Station, TX) will be used for data analysis.

1. **Privacy/Confidentiality Issues**

The participant research file will contain information concerning mental and physical health and experimentally derived data. All data collected in this study will be used specifically for research purposes. Should information that might have a bearing on the well being of participants be discovered, this information will be communicated to participants and, at the participant’s request, with their physician.

Electronic databases containing identifiable participant information will be password encoded. Written information containing participant identifiers (informed consent, lab results, participant payment, etc) will be stored in file cabinets in offices with the departments of Radiology and Psychiatry. Participants will be assigned an alphanumeric code that will be used to label all research data.

1. **Follow-up and Record Retention**

This pilot study is expected to last one year with data analysis continuing indefinitely. Records may be destroyed after data analysis is complete and all manuscripts are published, but records may be maintained indefinitely for future analysis. Emerging methods of analysis in fMRI research may permit the reanalysis of previously acquired data to extract new meaning.

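### The Aim 2 exercise tests use GEE on about 20 participants with no stated small-sample correction, and neither balanced exercise order nor a scan-period term is stated, so tests may be too liberal and effect sizes noisier than necessary.

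*Protocol*

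**What the plan says.** General statistical methods (section 10) assigns the Aim 2 tests to "general linear modeling (GLM) methods that incorporate Generalized Estimation Equations (GEE) for parameter estimation of correlated data". It explains the choice by flexibility and names two factors: "the mixed effects of between (cannabis vs. control) and within (prior exercise state". It does not say that the list of terms is complete. It names no variance estimator, reference distribution, small-sample correction, or period or sequence term.

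On size, the same section reasons from "Given proposed group sizes of 10 participants" with nothing missing, and Power Estimates says "we estimate 10 subjects per group as reasonable sample size". Study Procedures gives a larger number: "We plan to enroll 35 participants".

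On order, a footnote to Table 1 has "exercise in randomized order", and Enrollment/Randomization also says that the exercise intervention is randomized. Neither describes blocking or balancing. The Stimuli text balances image sets across participants against order effects, but says nothing about the order of the exercise conditions. Each participant has two scans (Table 1 footnote). General statistical methods and Power Estimates both intend the resulting effect sizes for planning a larger study.

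**The concern.** Ordinary GEE inference is justified by a large number of clusters. The clusters here are participants, about 20 of them. At that size the uncorrected robust variance is biased low and a normal reference has tails that are too thin. Both push p-values down and make intervals too narrow. The tests affected include the group x exercise interaction, which carries the hypothesis that exercise normalizes the users' brain response.

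Each person also sees the same kinds of cue at two scans, so a change from first to second scan (habituation, for example) is plausible. Different image sets do not remove it. If the numbers taking each exercise order are unequal, part of that change enters the exercise estimate, and unequal splits between groups carry part of it into the interaction. A pilot whose main product is effect sizes has reason to remove avoidable noise from them.

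**Working it through.** The protocol gives no effect size, standard deviation, power or alpha for Aim 2, so it has no figure to reproduce.

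**Inputs from the protocol:** 10 per group, 20 in total; two scans per person; GEE; group and exercise state as factors; randomized exercise order; 35 to be enrolled.

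**Assumptions:** two-sided alpha 0.05; in the simulations, Gaussian data with within-person correlation 0.5 and order effects of 0.3, 0.5 and 0.8 SD. The formula in step 1 does not depend on the correlation.

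**1. Type I error of the uncorrected robust z test.** With two scans per person and equal groups, the test works on within-person differences. The robust variance divides the residual sum of squares by n instead of n - k, where k is the number of group means fitted. So z = t x sqrt(n/(n - k)), and

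size = P(|t on n - k df| > 1.96 x sqrt((n - k)/n)).

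| Test | n | k | Threshold on the t scale | True size |
|---|---|---|---|---|
| Exercise or interaction, planned size | 20 | 2 | 1.96 x sqrt(18/20) = 1.859 | 7.9% |
| Exercise within one group | 10 | 1 | 1.96 x sqrt(9/10) = 1.859 | 9.6% |
| Exercise or interaction, 17 per group | 34 | 2 | 1.96 x sqrt(32/34) = 1.901 | 6.6% |
| Exercise or interaction, 8 per group | 16 | 2 | 1.96 x sqrt(14/16) = 1.833 | 8.8% |

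The correct threshold on 18 df is 2.101, so the interval at n = 20 is 1.859/2.101 = 0.885 of its proper width, about 11% too narrow.

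**2. Check by simulation** (exchangeable GEE, 10,000 runs per size). The uncorrected z test rejected 7.3% (exercise) and 8.1% (interaction) at 20 participants, 6.7% and 7.4% at 34, and 8.9% and 8.9% at 16. At 20 participants, scaling the variance by n/(n - p), with p = 4 model coefficients, and keeping z gave 4.9% and 5.3%. The Mancl-DeRouen covariance with t on n - 2 df gave 3.7% and 4.0%.

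**3. Order imbalance.** Let h be the change from first to second scan. If a of 10 people in a group take one order, that group's exercise estimate shifts by (2a - 10)/10 x h in absolute value. A 7:3 split gives 4/10 x h = 0.4h. Under simple randomization, P(7:3 or worse) = 2 x P(Binomial(10, 0.5) <= 3) = 0.344. The interaction shifts by 0.2h for each unit by which the two groups' counts differ. A difference of two or more (at least 0.4h) has probability 0.50.

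**4. Bias or noise?** Under simple randomization with no true exercise effect, the simulated mean exercise estimate stayed between -0.001 and 0.005 for all three order effects (4,000 runs each). Its spread rose:

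| Order effect (SD) | SD of estimate, sqrt((1 + h^2)/20) | Simulated, no period term |
|---|---|---|
| 0 | 0.224 | 0.221 |
| 0.3 | 0.233 | 0.231 |
| 0.5 | 0.250 | 0.254 |
| 0.8 | 0.286 | 0.281 |

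With a period term the simulated SD at 0.8 was 0.225. The variance without the term is (0.281/0.225)^2 = 1.56 times as large. The uncorrected z test still rejected 7.7-8.5%, so order noise does not add to the inflation in step 1.

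**5. The changes interact.** Adding a period term while keeping the uncorrected z test raised rejection to 8.6-9.9%. With Mancl-DeRouen and t it was 2.8-4.1%. Balancing order without a period term made the uncorrected z test of exercise fall to 6.8%, 5.0% and 2.0% as the order effect grew, because the order variation stays in the residual.

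**6. Which scan follows which condition.** Table 1 allows scans at Visits 1 and 3 or at Visits 2 and 3, and marks no exercise at Visit 1. The Scans text places imaging after a rest that follows exercise. The Exercise text puts the sessions at Visits 4 to 10, and the Table 1 footnote refers to Visits 4 to 12, where the table marks no scan. Exercise is described as vigorous and light, but Stimuli speaks of moderate and vigorous. If the first scan always comes without exercise, exercise state and scan order coincide. In the simulation a fixed order passed the whole order effect into the exercise estimate (0.30, 0.50 and 0.80), and no period term can separate the two.

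**The case against.** The protocol names GEE but neither the standard error nor the reference distribution. Such details often sit in a statistical analysis plan, and none is shown here. A reader might infer that the planned p-values are certainly too small. The document does not support that: the inflation is conditional on uncorrected inference, and a simple scaling of the variance largely removes it. What stands is that the protocol fixes the method and the sample size together, and the default form of that method is too liberal at that size.

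A reader might also infer that scan-order effects bias the exercise contrast, or that the model contains only group and exercise state. Neither follows. Order is randomized, so order effects average to zero, and the two factors are named as illustrations of what the method can handle. The 34% figure assumes simple randomization, which the protocol does not specify. The mock-scanner session may reduce novelty at the first scan, but it is optional and uses neutral images, so it does not address habituation to cannabis or food cues.

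Finally, this is a pilot, part of Aim 2 is descriptive, and a standard error that is too small leaves the point estimate unchanged. That limits the harm from the first half to tests and intervals. Order imbalance does act on the estimates themselves. Enrolling 35 would reduce the inflation without removing it.

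**Conclusion.** The point holds in a conditional and moderate form. With uncorrected standard errors and a z or Wald reference, a nominal 5% test has a true size of about 7-8% for exercise and for group x exercise at 20 participants. Within one group of 10 it is about 9.6%, and with about 34 analysed about 6.6%. This rests on two scans per person and approximately normal differences, and not on the within-person correlation.

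Scan order is a question of precision, not of systematic bias, provided that the order of the two scanned conditions really is randomized. The loss depends on an order effect the protocol does not quantify: over assumed values of 0.3 to 0.8 SD, the SD of the exercise estimate rises from about 0.22 to between 0.23 and 0.28. It matters here because these estimates are to power the next study. If the first scan is always without exercise, that proviso fails and the confounding is complete, so the visit schedule needs settling first.

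**What to change.** - Reconcile Table 1, the Exercise and Scans text, Stimuli and General statistical methods on which scan follows which exercise condition, and on whether the order of the scanned conditions is randomized for every participant.
- State a small-sample-corrected GEE covariance, such as Mancl-DeRouen, with a t reference. A linear mixed model with small-sample degrees of freedom serves equally well; the choice is a matter of preference.
- Add a scan-period term, together with the correction and not without it.
- Allocate the order of the exercise conditions in blocks within each group (5:5 in a group of 10). This must be set before enrolment, since analysis cannot restore balance afterwards.

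The cost is a few sentences, a blocked allocation list, one degree of freedom for period, and slightly wider intervals. In the simulations the corrected test was mildly conservative, at 3.7-4.0% without a period term and 2.8-4.1% with one.

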**Power Estimates**

Because this is a pilot study to demonstrate feasibility, we estimate 10 subjects per group as reasonable sample size as this group size is commonly well in fMRI pilot studies. A key outcome of this study will be the calculation of effect sizes that will inform the powering of subsequent, larger studies. Commercially available statistical software packages (NCSS and PASS, number Cruncher Statistical Systems, Kaysville, Utah; SPSS, Chicago, IL; Stata, College Station, TX) will be used for data analysis.

1. **Privacy/Confidentiality Issues**

The participant research file will contain information concerning mental and physical health and experimentally derived data. All data collected in this study will be used specifically for research purposes. Should information that might have a bearing on the well being of participants be discovered, this information will be communicated to participants and, at the participant’s request, with their physician.

Electronic databases containing identifiable participant information will be password encoded. Written information containing participant identifiers (informed consent, lab results, participant payment, etc) will be stored in file cabinets in offices with the departments of Radiology and Psychiatry. Participants will be assigned an alphanumeric code that will be used to label all research data.

1. **Follow-up and Record Retention**

This pilot study is expected to last one year with data analysis continuing indefinitely. Records may be destroyed after data analysis is complete and all manuscripts are published, but records may be maintained indefinitely for future analysis. Emerging methods of analysis in fMRI research may permit the reanalysis of previously acquired data to extract new meaning.

All information will be kept on computer storage disks or as paper for at least a 5-year period of time (including 5 years following the completion of these studies for data analysis). The computing centers of Vanderbilt University's Imaging Institute and the Division of Adult Psychiatry will be used to store and analyze the MRI data. Records will be coded by assigning an alphanumeric (not their initials) code for all documentation and data analysis sheets. The principal investigator, co-investigators, and research assistants working on the study will have access to the information. Identifying data such as name, address, etc. will be stored on computer using password-protection encryption and in locked files when in written format.

If paper records are to be destroyed those containing participant identifiers will be shredded directly or transferred to the hospital’s shredding service. If electronic data containing participant identifiers is to be destroyed, it will be disposed of using a medium-appropriate destruction method to prevent recovery. Data not containing participant identifiers will be disposed of by any convenient method.
